## Abstract

**Introduction:**

In current practice, fluid volumes administered to children following kidney transplant vary widely. Up to 52% of children experience fluid overload-related complications. Current fluid guidelines are not evidence-based and the optimal amount of fluid for children after transplant is not known. The aim of Randomised multiple centre trial of conservative versus LIberal fluid adMInisTration for children receiving a kidney tranSplant (LIMITS) is to determine whether relative limitation of fluid volume administered to children receiving kidney transplants is superior to liberal fluid volume administration.

**Methods and analysis:**

LIMITS is a pragmatic, open-label, UK-based, multicentre randomised controlled trial, with an internal pilot phase and integrated economic evaluation. A total of 140 children receiving kidney transplants will be randomised to receive either conservative postoperative fluid administration (maximum of 150 mL/m^2^/hour for no longer than 18 hours, followed by a fixed daily target of maximum 1.5 L/m^2^/day thereafter) versus the comparator of liberal postoperative fluid administration (fluid volume administered to replace urine output and insensible losses for at least 48 hours with target urine output >2 mL/kg/hour). The primary outcome is mean days at home in the first 30 days after kidney transplant. The primary outcome will be analysed using a mixed linear regression model adjusted for donor type (living vs deceased donor) and participant weight (<20 kg and ≥20 kg pretransplant) as fixed effects and transplant centre as a random effect. Cost-effectiveness will also be evaluated.

**Ethics and dissemination:**

The trial received Health Research Authority approval on 20 August 2025 (REC reference: 25/EE/0161, IRAS project ID: 354370). Findings will be presented to academic groups via national and international conferences and peer-reviewed journals. The patient and public involvement group will play an important part in disseminating the study findings to the public domain.

**Trial registration number:**

ISRCTN21516608.

STRENGTHS AND LIMITATIONS OF THIS STUDYThis is the first randomised controlled trial to evaluate optimal fluid volume management following paediatric kidney transplantation.A tailored Hospital Stay Experience Questionnaire will assess participants’ and families’ experience of kidney transplantation.Variation in current clinical practice between centres and clinicians makes standardisation of intraoperative fluid volumes unfeasible.Blinding was not considered feasible as the randomisation arm will be evident from fluid volumes administered.

## Introduction

 Kidney transplantation is the treatment of choice for children with end-stage kidney disease. Large volumes of fluid are routinely administered to children following kidney transplant. As a result, complications of fluid overload are frequent.^1^

Excess fluid can cause electrolyte imbalances such as hyponatraemia, which has resulted in reports of cerebral oedema, seizures and even death in severe cases.^2 3^ Fluid overload after transplant is associated with pulmonary oedema, hypertension, delayed wound healing, increased blood transfusions, delayed discharge from hospital.^4 5^ Fluid overload prolongs hospital admission which impacts children’s kidney dialysis and transplant care capacity and increases healthcare costs.^6^

Observational data in paediatric transplant recipients <20 kg and adult kidney transplant recipients have shown favourable outcomes with conservative fluid volume administration.^7 8^ Clinical trial outcomes in adults with sepsis support the non-inferiority of a restrictive fluid strategy compared with previous liberal fluid volumes.^9^ In adult kidney transplant recipients, the traditional practice of large volume fluid administration is no longer recommended^10^ as large fluid volumes do not reduce the proportion of adult grafts that fail or are slow to function as previously thought.^11^

This change in adult transplant practice has not been widely adopted for children despite frequent fluid overload related complications because of a view that the risks and benefits may differ in smaller children.^1^ Central to this is concern about delayed transplant function and/or thrombosis with using a conservative fluid approach. Existing data demonstrate a low risk of transplant thrombosis. One year graft survival in paediatric kidneys is 97% (deceased donor transplant) and 98% (living donor transplant), so the overall risk of graft thrombosis is <3% nationally as vessel thrombosis typically leads to graft loss.^12^

The aim of the LIMITS trial is to determine if relative limitation of fluid volume administered to children receiving kidney transplant is superior to liberal fluid volume administration with a primary outcome of mean days at home up to 30 days after transplant.

## Methods and analysis

### Study design and setting

LIMITS is a two-arm pragmatic, open-label randomised controlled trial comparing relative limitation of fluid volume administered (intervention) to liberal fluid volume administration (comparator) in paediatric kidney transplant recipients across 10 UK paediatric kidney transplant centres and three patient identification centres (box 1). The study started on 1 January 2025, with a projected completion of 31 December 2027. The first patient was recruited on 23 October 2025.

Box 1Participating UK paediatric kidney transplant centresHospitalBirmingham Children’s HospitalBristol Royal Hospital for ChildrenEvelina London Children’s HospitalGreat North Children’s HospitalGreat Ormond Street HospitalLeeds Children’s HospitalNottingham Children’s HospitalRoyal Belfast Hospital for Sick ChildrenRoyal Hospital for Children, GlasgowRoyal Manchester Children’s HospitalAlder Hey Children’s Hospital*University Hospital Southampton*University Hospital of Wales**Participant identification centre.

### Intervention and comparator

The intervention is a conservative postoperative fluid administration approach: fluid volume is capped at a maximum of 150 mL/m^2^/hour for no longer than 18 hours following transplant, followed by a fixed daily target of maximum 1.5 L/m^2^/day thereafter.

The comparator is a liberal postoperative fluid approach: fluid volume is administered to replace urine output and insensible losses for at least 48 hours with target urine output >2 mL/kg/hour. Diuretics are permitted at any time. This is reflective of current majority practice in the UK.^1^

The intervention is based on physiological rationale, existing data on fluid volume administration post kidney transplant, and preparation work regarding acceptability. Prolonged use of a urine output replacement regimen can perpetuate a fluid overloaded state by counteracting the physiological response to fluid overload—diuresis. This can lead to a vicious cycle perpetuating polyuria and fluid overload. Capping the duration of the urine output replacement regimen may shorten the time period during which fluid overload post-transplant can occur. A time cap of 18 hours was chosen to facilitate change of fluid strategy on the morning following transplantation to reflect real world practice of clinical decision-making on morning ward rounds.

### Outcome measures

The primary outcome measure for clinical effectiveness is mean days at home in the first 30 days after kidney transplant. The primary outcome measure for cost-effectiveness is kidney related costs within the study period which encompasses all costs incurred and implications for patient health within the study.

Secondary outcome measures are as follows:

Patient-reported experience of transplant hospital stay.Proportion of participants with systemic hypertension (systolic blood pressure above the 95th centile for age and height on 2 consecutive days) within 7 days after transplant.Proportion of participants with pulmonary oedema on chest X-ray within 7 days after transplant.Proportion of participants with severe acute hyponatraemia (defined as plasma sodium concentration <130 mmol/L) within 7 days after transplant.Proportion of participants receiving red blood cells within 7 days after transplant.Proportion of participants with transplant thrombosis in the postoperative period leading to graft failure within the first 30 days.Proportion of participants with delayed transplant function (dialysis within the first 7 days after transplant).Mean transplant function measured by estimated glomerular filtration rate (eGFR) at 3 months post-transplant.^13^

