### Treatment

Participants randomised to the intervention arm will receive usual fluids with the volume administered capped to a maximum rate of 150 mL/m^2^/hour for no longer than 18 hours following transplant, then reduced to a fixed daily fluid target not exceeding 1.5 L/m^2^/day thereafter until day 5. No specific urine output is targeted. Diuretics should not be administered intraoperatively nor postoperatively.

Patients randomised to the comparator arm will receive usual fluids to replace urine output plus insensible losses for at least 48 hours following transplant. Target urine output will be >2 mL/kg/hour and diuretics can be given as per the clinical team’s usual practice.

The choice of intravenous fluid (control or intervention) and decision to discontinue intravenous fluid and switch to enteral fluid will be determined by the treating clinician. All participants will receive routine clinical transplant care with no additional investigations or outpatient visits (figure 1, see onlinesupplemental files 1^4^ for schedule of procedures).

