### Data collection

Data will be collected and entered directly by the site personnel into a validated electronic data capture system.

Data collection will include baseline demographics, details of end stage kidney disease and operation details including graft placement, cold ischaemia time and intraoperative fluid volume. In the post-transplant admission period (7 days) data collection will include fluid balance, weight, blood pressure, chest X-ray, oxygen use, red cell transfusion requirement, medication, sodium, dialysis requirement and graft function and survival. Data collection postdischarge but within the first 30 days post-transplant will include date of hospital discharge, details of readmissions and outpatient visits, transplant thrombosis leading to graft failure and graft function, plasma creatinine and height. The economic evaluation data will capture time spent in ward areas of varying acuity, return to theatre, additional investigations and long-term disability. In the event of a patient withdrawal information will be recorded detailing date, who initiated withdrawal and reason.

Data quality will be ensured through specific checks, query management, audit trails and source data verification. Role-based access control and system security measures will be used to protect data integrity and confidentiality. Archiving will be authorised by the Sponsor following submission of the end of study report. Essential documents will be retained for a minimum of 5 years after completion of the trial. Detailed data management procedures are described in the Data Management Plan.

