### Safety

#### Adverse events and expected adverse drug reactions

Non-SAEs will not be reported. SAEs will be assessed by delegated individuals and the clinical trials unit (CTU) notified within 24 hours. SAEs will be monitored regularly by the DMC to ensure ongoing safety of trial participants. All SAEs will be followed up until resolution or stabilisation. All deaths will be reported as an SAE.

Certain SAEs are anticipated in this patient group and have therefore been excluded from trial safety reporting. These include surgical complications, infective complications, immunological complications and medication-related complications.

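### The 7-day blood-pressure and sodium outcomes are scored only in the direction of excess fluid, so early, non-serious signs of under-filling are collected but not compared between arms

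*Protocol article*

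**What the plan says.** Under Outcome measures, the article lists eight secondary outcomes. The blood-pressure outcome is hypertension, defined as "systolic blood pressure above the 95th centile for age and height on 2 consecutive days". The sodium outcome is "Proportion of participants with severe acute hyponatraemia (defined as plasma sodium concentration <130 mmol/L) within 7 days after transplant". Both cover the first 7 days, as do pulmonary oedema and red-cell transfusion.

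Under Treatment, the intervention arm is capped at 150 mL/m²/hour for at most 18 hours, "then reduced to a fixed daily fluid target not exceeding 1.5 L/m^2^/day thereafter until day 5. No specific urine output is targeted".

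Under Data collection, for the 7-day admission period, "data collection will include fluid balance, weight, blood pressure, chest X-ray, oxygen use, red cell transfusion requirement, medication, sodium, dialysis requirement" are recorded, together with graft function and survival.

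Under Adverse events and expected adverse drug reactions: "Non-SAEs will not be reported". Serious events go to the trials unit and are monitored by the DMC, apart from surgical, infective, immunological and medication-related complications, which are excluded from safety reporting.

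Under Monitoring compliance, the intervention arm has an upper limit only, 4700 mL/m² in 48 hours.

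**The concern.** Blood pressure and sodium can each depart from normal in two directions. The plan counts the direction that the Introduction attributes to too much fluid and leaves out the direction that too little fluid would produce. The arm under test is the one that limits fluid, so the direction left out is the one in which that arm would be expected to do worse.

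The stake is the balance of the safety report. The trial could show less hypertension and less hyponatraemia in the conservative arm and say nothing about hypotension or hypernatraemia, although the records to check both would be in the database. The Introduction says that conservative practice has not spread to children partly because risks and benefits may differ in smaller children. A two-directional account of the same measurements would speak to that more fully than a one-directional one. It would also give the DMC something to look at before graft events occur.

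**Working it through.** No stated figure is in dispute, so the check is mainly a comparison of sections.

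**1. Which direction each listed outcome covers**

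- Linked in the Introduction to excess fluid: hypertension, pulmonary oedema, hyponatraemia, red-cell transfusion (four outcomes).
- Linked in the Introduction to concern about conservative fluid: delayed transplant function and thrombosis (two outcomes). Three-month eGFR also bears on graft harm.
- Neutral: patient-reported experience.
- Low blood pressure, high sodium, weight loss or fluid deficit: no outcome.

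**2. Whether another route would report the missing signs by arm**

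- Adverse events: not if non-serious. Serious hypotension or hypernatraemia does not obviously fall in an excluded category, so it appears reportable.
- Compliance: the maximum intake over 48 hours is 150 × 18 + (1500/24) × 30 = 2700 + 1875 = 4575 mL/m². This agrees with the 4700 mL/m² limit. There is no lower limit, so a very low intake is not flagged in the intervention arm.
- DMC: the review at 28 randomised participants is of serious adverse events, with delayed function and thrombosis singled out.

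**3. Whether the data exist**

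Yes. All four variables (blood pressure, sodium, weight, fluid balance) are in the 7-day collection, so the opposite direction needs derived variables and no new measurements.

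**4. What added comparisons could show**

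The article gives no event rates for low pressure or high sodium, so the rates here are assumptions. With 63 per arm (the 126 evaluable participants divided by 2) and a two-sided 5% level, power is:

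- 5% vs 10%: 18%
- 5% vs 15%: 46%
- 5% vs 20%: 73%
- 5% vs 25%: 89%

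For precision, if 5% and 10% were observed, the standard error of the difference is √[(0.05 × 0.95 + 0.10 × 0.90)/63] = √(0.1375/63) = 0.047. The 95% interval is then 5 ± 1.96 × 4.7, or about −4 to +14 percentage points. That is informative as description and too wide for a formal claim.

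For comparison, the listed thrombosis outcome, taking 3% as the upper end of the Introduction's background risk, has about 36% power for 3% vs 10%. A null thrombosis result would be limited reassurance on its own.

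**The case against.** The strongest reply is that the outcome set already covers what the protocol names as the worry. The Introduction puts delayed function and thrombosis at the centre of concern about conservative fluid. Both are secondary outcomes and both are singled out for the DMC. Three-month eGFR is a continuous outcome compared between arms. The primary outcome is not one-sided either: under-filling that delayed discharge or caused readmission would reduce days at home. All of this stands, and it limits the point to early and non-serious harm.

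Three stronger readings are tempting and are not supported:

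- *Under-filling is not compared, or only end-stage harm can count against the conservative arm.* The outcomes just listed contradict this.
- *One-sided complication counts could produce the superiority conclusion.* Superiority is tied to days at home, not to a count of fluid complications.
- *The regimen implies a large daily deficit.* Such figures rest mostly on assumed inputs. Take a 15-kg child with assumed surface area (4 × 15 + 7)/(15 + 90) = 0.638 m², insensible losses of 300–400 mL/m²/day and a constant urine output of 4 mL/kg/hour. The daily balance at 1.5 L/m² is 957 − 1440 − (191 to 255) = −674 to −738 mL. But the first 18 hours at the permitted maximum give 1723 − 1080 − (144 to 191) = about +451 to +499 mL, which offsets most of one such day. Constant output also runs against the rationale under Intervention and comparator, which holds that replacement itself perpetuates polyuria. These numbers are illustrative only, and the point does not rest on them.

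Two further cautions are fair. Some diuresis is intended, so weight loss alone is not harm. The absence of any link to urine output is clear after 18 hours but less so before, because Intervention and comparator describes capping the duration of a urine-replacement regimen.

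Finally, this is a condensed article, and the full protocol or analysis plan may tabulate more. That is possible. Even so, the article itself sets out the outcomes and their direction, and an analysis plan usually governs how listed outcomes are analysed.

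**Conclusion.** The point holds in a narrow form. As the outcomes are written, direct signs of over-filling are reported by arm and direct signs of under-filling are not, although the same 7-day records contain both. The gap concerns early and non-serious harm. It does not undermine the primary analysis, and graft consequences and serious events have their own routes.

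Its clinical size cannot be given, because the documents contain no rates for low blood pressure or high sodium. The power figures rest on assumed rates and 63 evaluable participants per arm. The conclusion also assumes that no unshown document already provides opposite-direction safety summaries. If one does, the point is met. This is an inexpensive improvement to the balance of the safety report, not an error that threatens the trial.

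**What to change.** Add three descriptive safety outcomes over the same 7 days, reported by arm with confidence intervals beside the overload outcomes:

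1. Low systolic pressure, defined symmetrically with the hypertension outcome (for example, below the 5th centile for age and height on 2 consecutive days).
2. Plasma sodium above an upper limit that the investigators prespecify.
3. Largest fall in weight below the pretransplant value, read together with fluid balance because some diuresis is intended.

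Include them in the DMC tables, including the review at 28 participants. With about 14 per arm at that point (28/2), simple counts and ranges are enough.

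The cost is wording in the protocol and analysis plan and three derived variables. The downside is three more low-powered comparisons, so they should be labelled descriptive, with no formal tests. Nothing here changes the fluid regimen, the sample size or the data collected.

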### Eligibility criteria

#### Inclusion criteria

Children <18 years of age at the time of transplantation with valid informed consent.Children receiving a kidney only transplant from either a living or deceased donor, in a participating centre.

#### Exclusion criteria

Multiorgan transplant recipients.

### Screening, recruitment and randomisation

All patients <18 years old awaiting kidney transplantation, from a living or deceased donor, will be screened for participation in participating sites plus three participant identification centres. The trial will be discussed by the clinical team during the pretransplant preparation period. The potential benefits and risks of study participation are included in age stratified study information sheets.

Under Clinical Trial Regulations, a person under the age of 16 years is deemed to be a ‘minor’ and an appropriate adult must give consent on behalf of the child. However, the wishes of the child must form part of the decision-making process and the child’s assent will be sought and recorded. For young people aged 16–18 years their informed consent will be taken (see onlinesupplemental files 1^4^ for copies of consent and assent forms). Any person aged 16 or over who lacks capacity to consent will not be considered for participation. Informed consent and patient assent will be taken by the Principal Investigator (PI) or delegated individual.

Participants will be randomised in a 1:1 ratio to the intervention and control groups via an online system (Sealed Envelope) which produced the randomisation list. Randomisation will be stratified by transplant centre and donor type (deceased vs living donation) and will further be balanced within blocks of varying, undisclosed sizes.

### Treatment

Participants randomised to the intervention arm will receive usual fluids with the volume administered capped to a maximum rate of 150 mL/m^2^/hour for no longer than 18 hours following transplant, then reduced to a fixed daily fluid target not exceeding 1.5 L/m^2^/day thereafter until day 5. No specific urine output is targeted. Diuretics should not be administered intraoperatively nor postoperatively.

Patients randomised to the comparator arm will receive usual fluids to replace urine output plus insensible losses for at least 48 hours following transplant. Target urine output will be >2 mL/kg/hour and diuretics can be given as per the clinical team’s usual practice.

The choice of intravenous fluid (control or intervention) and decision to discontinue intravenous fluid and switch to enteral fluid will be determined by the treating clinician. All participants will receive routine clinical transplant care with no additional investigations or outpatient visits (figure 1, see onlinesupplemental files 1^4^ for schedule of procedures).

**Figure 1 F1:**
[figure not shown]
LIMITS study flow chart. *No diuretics to be given in the capped fluid group intraoperatively.

Each participant and their family have the right to withdraw from the trial at any time. The investigator may discontinue a participant from the trial at any time if considered necessary for any reason.

### Patient Reported Experience Measures: Hospital Stay Experience Questionnaire

A patient-reported experience questionnaire has been developed for this trial to better understand the patient and family experience of their transplant hospital admission. On the day of discharge the relevant version of the Hospital Stay Experience Questionnaire (HSEQ) will be completed anonymously by both the participants and their parent(s)/carer(s). Younger children or those with a learning disability may receive assistance with completion from their parent(s)/carer(s). For children under the age of 7, a parent/carer HSEQ only will be completed.

